#### Patients not recruited into the study

Data will be available from the screening questionnaire for those patients who prefer not to participate in the randomised trial or who are excluded as per the study protocol, but who agree to complete the monthly diaries and end of study booklet. Using this data it will be possible to check the representative nature of the study population and the discriminatory power of the screening questionnaire. Those subjects who prefer not to take part in the study at either level will not be contacted any further. They will have access to usual care through their GPs/primary care teams.

### Randomisation

After giving informed consent patients will be randomly allocated (1:1 ratio) to either the intervention group or to the control group. Randomisation will be made by telephone to the TRDSU who will be blind to the identity of the patient, and will use a computer program (Stata) to carry out stratified block randomisation based on study centre (Nottingham, Derby).

### Treatment

#### Intervention arm

The intervention arm will be invited to attend the day hospital for an assessment and any subsequent intervention, including:

##### Medical assessment and treatment performed by a clinician

History (including medications) [standard format]; a full physical examination including visual acuity and orthostatic blood pressure measurement; laboratory tests where indicated; 12 lead ECG and where appropriate a neurovascular assessment (carotid sinus massage and tilt tests). Treatments will vary according to the medical diagnoses made and will include medication review, appropriate referral to an optician or ophthalmologist for visual impairment and referral to other specialists where necessary.

##### Physiotherapy assessment and individualised therapy programme conducted by a physiotherapist

Assessment for gait, balance, mobility and muscle strength (using the Tinetti[15] method and measurement of ankle dorsiflexion strength[16]). Interventions will include gait re-education and functional training programme using the principles of Koch[17], and muscle strengthening exercise programme based on a modified Dunedin protocol[10], and where indicated the provision of an appropriate walking aid. The feet and footwear will be assessed for abnormalities that could impair gait and appropriate referrals will be made to a chiropodist or an orthotist. The number and timings of follow up visits at the day hospital for further assessment and therapy and telephone calls to check compliance with the programme will depend on the individualised needs of the participants.

##### Occupational therapy assessment and modifications, performed by an occupational therapist

Interview with the participant using a standardised checklist to investigate home hazards[18]. Where necessary, a home visit will then also be performed. Participant's functioning will be assessed using a standard activities of daily living measure[19]. Modification of identified environmental hazards will be suggested according to published criteria[18].

#### Control arm

In addition to the falls prevention leaflet, the control group will receive all routine care provided by their primary care service. This may or may not include referral to secondary care, depending on the GP's judgement. At present, there are primary care falls prevention services being developed, but in an inconsistent manner. Participation in the control arm may include referral to such services as part of normal practice, but these referrals will not constitute part of the trial protocol. Patients in the intervention arm will be asked not to participate in the primary care falls prevention services for the duration of the trial. Assuming the trial does not show a detrimental effect from the day hospital intervention, the control group will be offered day hospital attendance at the end of the trial.

### Contamination

Pilot data from the Nottingham Community Osteoporosis (NOCOS) study[20] suggest that very few older patients identified as fallers are referred to secondary care or other agencies for a falls assessment (personal communication with Trial Co-ordinator). Although contamination between groups is a potential limitation, our previous experience suggests this is unlikely to be an important issue. We will specifically check to see if any of the control group have attended secondary care services for a falls evaluation. Currently all referrals to the primary care falls prevention services are centralised within each primary care trust; through checking with these centres, we will be able to ascertain who in the control group received a primary care based intervention. We will also use this point of contact to ensure that those in the day hospital arm of the trial are not also receiving a community intervention or follow-up.

### Withdrawal

Participants wishing to withdraw from the study will be free to do so at any stage, without any detriment to their usual care.

### Concurrent treatment

There are no other falls prevention studies running in this area at present that might be relevant. Community falls prevention programmes are being developed, but we will liaise with these groups to ensure that the day hospital group are not put into these services. The control group will be able to access these services in the usual fashion.

### Data analysis

#### Power and sample size

With an expected rate of falls of 2/year per person[11], and an over dispersion parameter of 1.5 a clinically important risk reduction of 24% to 1.5 falls/year can be detected with 80% power and 5% significance (two-sided) in a trial of 160 participants in each arm giving a trial size of 320. This assumes a Poisson distribution with over dispersion. If the fall rate was 1/year per person[10] a risk reduction of 33% could be detected with this sample size (not a high risk population). To allow for an attrition rate of 20% (see below) we will recruit a total of 400 participants. To achieve this, 3125 subjects will need to be screened, of whom 40% may be at high risk of falls. Of these 1250, 20% are likely to be ineligible leaving 1000 potential participants of whom it is thought that 40% will agree to take part. This sample size will also have 80% power at the 5% significance level to detect a reduction of one third in the proportion of people with one or more falls, with an expected proportion with one or more falls of 50% at 12 months.

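### The 50% faller proportion, if it belongs to the 2 falls/year population as it appears to, rules out the over-dispersion of 1.5 behind the 80% power claim

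*Protocol article*

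**What the plan says.** All the figures stand in one paragraph of the protocol article, under Power and sample size.

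- Primary outcome: "With an expected rate of falls of 2/year per person[11], and an over dispersion parameter of 1.5 a clinically important risk reduction of 24" per cent, to 1.5 falls/year, is the target effect. This "can be detected with 80% power and 5% significance (two-sided) in a trial of 160 participants in each arm".
- Distribution: "This assumes a Poisson distribution with over dispersion".
- Alternative rate: at 1 fall/year a 33% reduction is said to be detectable with the same numbers. The text adds in brackets that this is not a high-risk population.
- Secondary outcome: the same sample is said to have 80% power for a one-third reduction in the proportion of fallers, "with an expected proportion with one or more falls of 50% at 12 months".

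The paragraph does not define the 1.5 or link the 50% to either rate. Elsewhere, Subject definition restricts the trial to people at high risk of falling. Univariate and multivariate analyses calls over-dispersion likely and names negative binomial regression for that case.

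**The concern.** The mean, the dispersion and the proportion with no falls are not free of one another. If half a population never falls and the mean is 2, those who do fall average 4 each, and that split alone creates a large variance. The paragraph appears to describe one high-risk sample by a mean of 2, a dispersion of 1.5 and 50% fallers, and those three cannot all be true.

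The rate of falling is the primary outcome and the main hypothesis. If the dispersion is understated, the trial can reliably detect only a larger effect than the protocol says. A null result read against the stated 80% power would then carry more weight against the day hospital than the design supports.

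**Working it through.** **Inputs** (Power and sample size): control mean m1 = 2; intervention mean m2 = 1.5 (a 25% reduction, although the text says 24%); over-dispersion 1.5; two-sided 5%; 80% power; 160 per arm; 50% with at least one fall. Follow-up is 12 months (Outcome measurements).

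**Formula.** With variances v1 and v2, let S = v1/m1² + v2/m2². Then n per arm = K·S / [ln(m2/m1)]², where K = (1.960 + 0.842)² = 7.849 and [ln 0.75]² = 0.0828, so n = 94.84·S. Power at 160 per arm = Φ(0.2877·√(160/S) − 1.960).

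**Step 1: reproduce the plan's figure.** Read 1.5 as variance/mean.
- Variance = 1.5 × mean in both arms: S = 0.75 + 1.00 = 1.75, n = 166, power 79%.
- Negative binomial with α = 0.25 (variance/mean 1.5 at mean 2): S = 0.75 + 0.917 = 1.667, n = 158, power 80%.

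So 160 reproduces. Other readings do not give it: a negative binomial with α = 1.5 needs 395 per arm (43% power at 160), and one with shape 1.5 needs 237 (63%).

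**Step 2: is 1.5 compatible with mean 2 and 50% fallers?** For a count with mean m and proportion p0 at zero, the variance is smallest when every faller has the same count, giving variance ≥ m²·p0/(1 − p0). With m = 2 and p0 = 0.5, fallers average 4, so variance ≥ 0.5 × 4² − 2² = 4 and variance/mean ≥ 2. A ratio of 1.5 is impossible.

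The other way round, mean 2 and ratio 1.5 give a variance of 3 and E[X²] = 3 + 4 = 7. Then P(X > 0) ≥ 2²/7 = 57%. With whole-number counts (fallers having 3 or 4 falls) the minimum is 7/12 = 58%. Under a negative binomial, P(0) = 1.5⁻⁴ = 0.198, so about 80% fall.

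**Step 3: power at 160 per arm for 2 versus 1.5 under the resulting dispersions.**

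| Assumption | S | n per arm for 80% | Power at 160 | Detectable reduction |
|---|---|---|---|---|
| Half of each arm falls; all fallers in an arm have the same count (4 or 3) | 1 + 1 = 2 | 190 | 73% | 27% |
| Ratio 2 in control, negative binomial variance (α = 0.5) | 1 + 1.167 = 2.167 | 205 | 70% | 28% |
| Ratio 2 in both arms | 1 + 1.333 = 2.333 | 221 | 66% | 29% |
| Negative binomial with mean 2 and 50% fallers | 3.160 + 3.327 = 6.486 | 615 | 30% | 44% |

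For the last row, (1 + 2α)^(−1/α) = 0.5 gives α = 2.66, a variance/mean of 1 + 2 × 2.66 = 6.3. A run of 500 simulated trials gave 28.8% power. The last column solves n = 160 for the reduction; in the first row, |ln(1 − r)| = √(7.849 × 2/160) = 0.313, so r = 27%.

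**Step 4: the 1/year alternative.** At mean 1 with 50% fallers the bound is variance/mean ≥ 1, so 1.5 is allowed; a negative binomial with that ratio has 1 − 1.5⁻² = 56% fallers. Power at 160 per arm for the stated 33% reduction is about 75–78% at ratio 1.5. It is about 67–68% at the negative binomial value matching 50% fallers (α = 1, ratio 2), where the detectable reduction is about 38%.

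**Step 5: the secondary claim.** On its own terms it is sound: 50% versus 33.3% needs 137 per arm (148 with continuity correction), and 160 gives 86% power.

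**The case against.** The strongest reply is that the conflict depends on a pairing the protocol never states. The 50% comes at the end, as input to a separate binary calculation, and at 1/year it sits comfortably with 1.5. That stands: the pairing with 2/year is inferred. It is still the natural one, since the trial enrols high-risk people and the text sets 1/year apart as not high risk. Moving the 50% to 1/year also leaves the stated 33% reduction somewhat short of 80% power (Step 4).

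A reader might infer that the sample-size arithmetic is wrong. It is not: 160 follows from its own inputs, and the secondary claim holds too. The fault lies between assumptions, and if 1.5 is kept and the 50% changed, 160 survives.

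A reader might also conclude that the trial has 30% power, or that a ratio of 1.5 means 80% fallers. Both hold only under a negative binomial. That is the planned analysis model, but the sample-size paragraph assumes only an over-dispersed Poisson. Free of any model, the conflict is 50% against at least about 58% fallers.

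Finally, 400 are to be recruited and leavers contribute falls up to withdrawal. If all 400 were followed for the full year, power at 200 per arm would be 82% in the artificial best case, 76% with ratio 2 in both arms and 36% under the fitted negative binomial. But the extra 80 are there to cover 20% attrition, so this is not the planned position.

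The planned regression estimates dispersion from the data, so this point concerns the power claim and leaves the validity of the primary analysis untouched.

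**Conclusion.** The point holds, conditional on the 50% describing the 2 falls/year population. On that reading the control-arm variance/mean ratio is at least 2, whatever the distribution, and the 1.5 supporting the 80% power claim cannot be right. The size of the shortfall depends on assumptions the protocol does not settle. With half of each arm falling, power for 2 versus 1.5 at 160 per arm runs from about 73% as a ceiling, through about 66–70% at a ratio of 2, to about 30% under the fitted negative binomial. The ceiling needs every faller in an arm to have the same count, which will not happen in practice. The lower end rests on fitting one model to two rounded planning figures. It is not a knife-edge result, however: under a negative binomial at mean 2, 60% fallers gives about 42% power and 70% gives about 60%.

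**What to change.** Revise the Power and sample size paragraph, leaving the number of participants as it is.

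1. State that 1.5 is a variance/mean ratio, and say which fall rate the 50% belongs to.
2. Reconcile the two in one of these ways:
   - Keep 2/year and 50% fallers, use a dispersion consistent with them (variance/mean of at least 2; about 6.3 under a negative binomial), and restate either the power for a 25% reduction at 160 per arm (about 30–73%, depending on the distribution) or the detectable reduction (about 27–44%).
   - Keep 2/year and 1.5, raise the expected proportion of fallers (at least about 58% under any distribution, about 80% under a negative binomial), and restate the secondary power claim on that basis.

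The cost is the rewording of one paragraph. Under the first option the stated power for the primary outcome becomes less favourable; under the second it stands, but the expected proportion of fallers has to be defended afresh.

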#### Data monitoring and analysis

Data will be double entered into Access to check data entry validity and analysis performed using SPSS (version 11) and Stata (version 8). Intention to treat analysis will be used. Analysis will performed according to the pre-specified analysis plan.

#### Univariate and multivariate analyses

For the primary analysis, Poisson regression or if there is over-dispersion (likely), negative binomial regression will be used to estimate the incidence rate ratio comparing the rate of falls between the two randomised groups during the follow-up period. The number of falls will be the numerator and length of follow-up the denominator.

Secondary analysis will compare the following outcomes between treatment arms:

a) The proportion of people with one or more falls over the follow-up period, using logistic regression

b) Time to first fall using survival analysis

c) the proportion of people with injurious falls using logistic regression

d) the proportion of people institutionalised at 12 months using logistic regression

e) Impact on disability, quality of life, fear of falls, and use of health services will be assessed using linear regression models with transformations if necessary, although some of these comparisons will be underpowered.

f) Deaths will be compared between the two groups. The analysis will be survival analysis using Cox proportional hazards model.

All analyses will adjust for the strata used in the randomisation procedure. If there are other important baseline differences, for example in age or number of previous falls, multivariate analysis will be used to adjust for them.

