### Outcome measurements

#### Definition of primary and secondary outcomes

Primary outcome: rate of falling over the 12 month follow-up period.

Falls will be recorded by giving each participant a diary and reply paid envelopes. The definition of a fall given to subjects in this study will be 'inadvertently coming to rest on the ground or other lower level with or without loss of consciousness and other than as a consequence of sudden onset of paralysis, epileptic seizure, excess alcohol intake, or overwhelming external force' (PROFET[11]).

Participants will be asked to record falls in the diary, along with the outcome (saw GP, phoned ambulance, sent to hospital, injuries). The diaries will be mailed back to the research team at the end of every month. Participants will be contacted via telephone by the "blinded" assessor at the end of each month to encourage return of the diary. Falls will be monitored until, withdrawal from study, death or end of 12 month follow up, which ever event occurs first.

Secondary outcomes:

1. Proportion of people with single or recurrent falls (>1)... defined as above

2. Fall-related injuries: fracture, serious sprain requiring immobilisation in plaster, joint dislocations, head injury requiring hospitalisation, and lacerations requiring suturing

3. Disability: Nottingham Extended Activities of Daily Living Scale; Barthel index of daily living; Quality of life: Falls Efficacy Scale and EuroQoL-5

4. Institutionalisation and use of health services: residency and diary information

5. Cost analysis

6. Screening tool... defined by sensitivity/specificity as well as positive and negative predictive values

7. Deaths will be checked against PCT records and measured as proportions

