#### Ascertainment of outcomes

The principal method will be self-reporting using the diary. This will contain a section on falls and the outcomes (carried on as usual, called for help, waited for someone to help, called GP, called ambulance, taken to hospital, nature of any injury). Additionally, there will be a section recording health service utilisation, covering primary care contacts and hospital admissions.

The self-reported data will be cross referenced where possible through access to GP records and hospital information systems. For hospital admissions, access to the case notes will be requested and the notes reviewed. This level of information will allow a more accurate ascertainment of events as well as the costs associated. Information on falls-related drug treatment (such as bone protection therapy) will be obtained from the GP records. These data will be collected by the project manager and project officer on standardised forms. The data collection will be subject to internal audit to ensure accurate and consistent data recording and avoid intraobserver and interobserver bias.

Institutionalisation data will be available from practice registers. Those who change practice as a result of changing address will be traced through the primary care trusts.

Disability and quality of life will be self reported by study participants. They will be asked to complete the Nottingham extended activities of daily living scale (NEADL)[24], Barthel index of Daily Living, EuroQol[25] and the falls efficacy scale[26]. These will be posted at the end of one year, along with reply paid envelopes. Non-responders will be sent a written reminder and if necessary a follow-up phone call ('hot pursuit').

EuoQol is included to facilitate cost-effectiveness and cost-utility calculations, but the Falls Efficacy Scale (FES) is a more sensitive measure of quality of life in this population, hence its inclusion[27]. The FES has been validated in the UK as both a face to face and self completed questionnaire[27]. The intraclass correlation coefficient is 0.58, suggesting fair agreement when used as a postal questionnaire. Both the Barthel index and the NEADL are well validated measures of functional ability and can be used as a postal questionnaire[24].

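### The primary fall rate is divided by time in the trial, not diary-covered time: missing diaries understate the rates, and bias the rate ratio if diary return differs by arm

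*Protocol article*

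**What the plan says.** All references are to the protocol article.

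- **Outcome.** Under Definition of primary and secondary outcomes: "Primary outcome: rate of falling over the 12 month follow-up period".
- **Model.** Under Univariate and multivariate analyses, Poisson regression is planned or, if the counts are over-dispersed, "negative binomial regression will be used to estimate the incidence rate ratio comparing the rate of falls between the two randomised groups".
- **Denominator.** The same section adds: "The number of falls will be the numerator and length of follow-up the denominator".
- **End of follow-up.** Under Definition of primary and secondary outcomes: "Falls will be monitored until, withdrawal from study, death or end of 12 month follow up, which ever event occurs first". A missed diary is not among these events.
- **Source of falls.** Under Ascertainment of outcomes: "The principal method will be self-reporting using the diary". On timing: "The diaries will be mailed back to the research team at the end of every month".
- **Safeguards.** Participants are telephoned by a blinded "assessor at the end of each month to encourage return of the diary", and Table 1 (Trial documentation) lists a diary completion reminder. There is also a second source: "The self-reported data will be cross referenced where possible through access to GP records and hospital information systems".

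The protocol does not say how a month without a diary enters the rate. It gives no expected diary return, overall or by arm. The 20% attrition allowance under Power and sample size is not a diary return rate.

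**The concern.** The two halves of the primary rate can cover different periods. The denominator runs for as long as a person stays in the trial. The numerator depends mainly on diaries that may or may not come back. Someone who skips or stops sending diaries without withdrawing goes on contributing time, but their self-reported falls cannot be counted.

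Two things are at stake. First, the absolute rates are understated. This carries into Economic analyses, where falls prevented is a principal outcome. Second, the incidence rate ratio is at risk if diary return is unequal. That is plausible because participants are told their allocation. The intervention arm may also have repeat day hospital visits and compliance calls (physiotherapy section), whereas the control arm has a leaflet and usual care. The bias could go either way.

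**Working it through.** **Inputs from the protocol (Power and sample size):** control rate 2.0 falls per person-year, target 1.5, so a rate ratio of 1.5/2.0 = 0.75; over-dispersion 1.5; 160 per arm; two-sided 5%; 80% power; 400 recruited after 20% attrition.

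**Assumed input:** diary return by arm, taken between 80% and 95%.

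**1. The plan's own figure.** Reading 1.5 as a variance inflation factor and taking one year per person:

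- Log rate ratio form: n = 1.5 × (1.960 + 0.842)² × (1/2.0 + 1/1.5) / (ln 0.75)² = 166 per arm.
- Square-root form: n = 1.5 × (1.960 + 0.842)² × 0.5 / (√2.0 − √1.5)² = 164 per arm.
- Power at 160 per arm, log form: 78.5%.
- 320 / 0.8 = 400.

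The stated 160 is reproduced closely. It assumes that falls are fully observed.

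**2. Effect of missing diaries.** Let r be the share of follow-up months with a diary, with months missing independently of falls and no falls recovered from records. Dividing by full follow-up:

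- observed rate = true rate × r
- observed rate ratio = true rate ratio × r(intervention) / r(control)

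Dividing by diary-covered time, r cancels within each arm and the true ratio is recovered.

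If records recover a share s of the falls in missing months, the factor becomes [r(I) + s(1 − r(I))] / [r(C) + s(1 − r(C))], which moves towards 1 as s rises. The figures below take s = 0, so they are upper limits for a given gap in return.

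**3. Equal return.** The ratio stays at 0.75.

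| Return, both arms | Observed rates | Difference | Power at 160 per arm |
|---|---|---|---|
| 100% | 2.0 and 1.5 | 0.50 | 78.5% |
| 90% | 1.8 and 1.35 | 0.45 | 74.2% |
| 80% | 1.6 and 1.2 | 0.40 | 69.2% |

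The power loss comes from unrecorded falls, and a different denominator does not restore it. The understated difference does come from the denominator: at 80% return, cost per fall prevented would be overstated by 0.50/0.40 = 1.25, or 25%, if costs are held fixed.

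**4. Unequal return.**

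| Intervention / control return | Factor | True ratio 1.00 | True ratio 0.75 |
|---|---|---|---|
| 90% / 85% | 1.059 | 1.06 | 0.794 |
| 85% / 90% | 0.944 | 0.94 | 0.708 |
| 90% / 80% | 1.125 | 1.13 | 0.844 |
| 80% / 90% | 0.889 | 0.89 | 0.667 |
| 95% / 85% | 1.118 | 1.12 | 0.838 |
| 85% / 95% | 0.895 | 0.89 | 0.671 |

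On the log scale, the 95%/85% case is ln 1.118 / |ln 0.75| = 0.111/0.288 = 0.39 of the planned effect.

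**The case against.** Person-time as exposure is the standard choice for these models, so the quoted sentence is not an error in itself. The protocol refers to a pre-specified analysis plan that is not shown. That plan may define length of follow-up as observed diary time, and the handling of skipped diaries is often left to it. This limits the point but does not remove it: the protocol names a denominator and says when follow-up stops, and taken together these mean time in the trial.

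A reader might infer three stronger claims that the documents do not support.

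- **Every missing diary is scored as a fall-free month.** No sentence says so. It is only the consequence of the plain reading for self-reported falls.
- **Falls are known only from returned diaries.** GP and hospital records are a second source. They would mainly show falls that led to care, however, and the diary also covers falls after which the person carried on as normal.
- **The rate ratio is biased as the plan stands.** With equal return unrelated to falls, it is not.

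The monthly call and the reminder are not restricted to one arm, which should help to keep return similar. The stated purpose of the call is diary return, though; collecting falls by telephone is not mentioned. Finally, the gaps in return used above are illustrative and say nothing about what this trial would see.

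**Conclusion.** The point holds in conditional form. As written, the denominator of the primary rate is not tied to the time over which falls were ascertained, and incomplete diary return lowers the absolute rates in proportion, apart from falls recovered from records. The rate ratio is unaffected by equal return that is unrelated to falls. With a 10-point gap between arms it shifts by about 11% to 13%, in a direction set by which arm returns more diaries; with a 5-point gap it shifts by about 6%.

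These sizes rest on assumed return rates, on months missing independently of falls within each arm, and on no recovery from records. The change is worth making because the outcome is primary and the correction is small. Confidence is moderate, because the unseen analysis plan may already settle the definition.

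**What to change.** In Univariate and multivariate analyses, replace length of follow-up by ascertained time: the model offset is the log of the time for which fall status was established, meaning months covered by a returned diary or months for which fall status was otherwise obtained. A month should qualify only through a source that could have shown either falls or no falls. Otherwise, months would be added because a record happened to show a fall, and the rate would be pushed up.

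Report diary-months returned by arm. Add a sensitivity analysis that uses calendar follow-up with record-identified falls included, or one that imputes the missing months.

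The cost is a few sentences and no new data collection. Monthly chasing and the reminder form imply that diary return is tracked, but the protocol does not say so; this should be confirmed. The downside is that the main analysis assumes similar fall rates in missing and observed months. If people skip diaries when nothing has happened, rates would be overstated; if they skip after a serious fall, rates would be understated. The sensitivity analysis probes this assumption but cannot fully resolve it, since ordinary imputation makes a similar one.

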### Secondary research questions

1. Can the above intervention reduce the proportion of people with single or recurrent falls (>1)?

2. Can the above intervention reduce fall-related injuries (including fractures)?

3. Can the above intervention reduce disability and improve quality of life?

4. Can the above intervention reduce institutionalisation and the need for the use of health services?

5. Is the intervention cost-effective and might it lead to overall cost-savings?

6. Can a screening questionnaire used in primary care reliably distinguish between low and high risk of falling?

7. Is there any difference in deaths between the two groups?

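### Injurious falls have no analysis that allows for early end of follow-up, and recurrent falls (more than one), a named secondary outcome, have no listed analysis

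*Protocol article*

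**What the plan says.** All references are to the Protocol article.

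- **Follow-up.** Under Outcome measurements, falls are monitored to the first of withdrawal, death or 12 months. Power and sample size states: "To allow for an attrition rate of 20% (see below) we will recruit a total of 400 participants".
- **Primary analysis.** Univariate and multivariate analyses uses length of follow-up as the denominator of the fall rate.
- **Secondary analyses, same section.** Item (a) is "The proportion of people with one or more falls over the follow-up period, using logistic regression". Item (b) is a survival analysis of time to first fall. Item (c) is "the proportion of people with injurious falls using logistic regression". Item (d) is institutionalisation at 12 months. In item (e), disability, quality of life, fear of falling and service use "will be assessed using linear regression models with transformations if necessary". Item (f) compares deaths with a Cox model.
- **Recurrent falls.** Secondary question 1 asks "Can the above intervention reduce the proportion of people with single or recurrent falls (>1", the bracket setting the cut-off at more than one fall. Secondary outcome 1 repeats it. No item from (a) to (f) compares people with two or more falls.
- **Time frame of the faller proportion.** Power and sample size assumes "an expected proportion with one or more falls of 50% at 12 months", whereas item (a) refers to the follow-up period.

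**The concern.** A proportion of fallers at 12 months and a proportion over whatever follow-up each person had are the same quantity only if nobody leaves early. The protocol expects one in five to be lost. It corrects for time observed in the primary analysis, but not in the logistic regressions of (a) and (c). If someone who leaves fall-free at two months enters (a) or (c) as a non-faller, the arm that loses more people appears to have fewer fallers.

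Differential loss is plausible here. Participants are told their arm, the intervention arm is asked to attend the day hospital, and controls are offered it only after outcome data are collected. Which way any difference would run is inference.

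The recurrent-falls gap is a different kind of problem. A stated secondary question has no analysis assigned to it, so the method would be chosen later, possibly with the data in view.

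**Working it through.** **1. The plan's own figures.** Inputs: "can be detected with 80% power and 5% significance (two-sided) in a trial of 160 participants in each arm", and for fallers "This sample size will also have 80% power at the 5% significance level", with a one-third reduction from 50% to 33.3%.

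n per arm = [1.96·√(2·p̄·q̄) + 0.842·√(p1q1 + p2q2)]² / (p1 − p2)², with p̄ = 0.4167:

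[1.96 × 0.6972 + 0.842 × 0.6872]² / 0.1667² = 136.2, so 137 per arm (148 with continuity correction).

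Power at 160 per arm is 86% (about 83% with correction), so the stated 80% is met with room to spare. Attrition: 320 / 0.8 = 400, as stated. The sample size is therefore not the problem.

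**2. Which items have follow-up that can differ between people?**

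| Item | Quantity | Allowance for early end of follow-up |
|---|---|---|
| (a) | any fall, over follow-up | none in (a); (b) covers the same event |
| (b) | time to first fall | yes, censoring |
| (c) | injurious fall | none, and no companion analysis |
| (d) | status at 12 months, from practice registers | not applicable |
| (e) | scales posted once at one year | not applicable; loss is missing data |
| (e) | service use, accumulating | none stated |
| (f) | deaths, Cox model | yes, censoring |

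**3. Size of the bias if early leavers are counted on observed time.** Assumptions: constant hazard; 12-month risk p = 0.50 in both arms (the protocol's control figure); a fraction *a* leave, uniformly over the year and unrelated to falling; attrition splits chosen around the planned 20%.

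Hazard λ = −ln(0.5) = 0.693. Mean risk observed in leavers = 1 − 0.5/0.693 = 0.2787.

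Observed proportion = (1 − a) × 0.5 + a × 0.2787.

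| a | 10% | 15% | 20% | 25% | 30% |
|---|---|---|---|---|---|
| observed | 47.8% | 46.7% | 45.6% | 44.5% | 43.4% |

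Odds ratio, intervention against control, with no true effect:

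- 20% and 20%: 1.00.
- 25% and 15%: (0.4447/0.5553) / (0.4668/0.5332) = 0.91; reversed, 1.09.
- 30% and 10%: (0.4336/0.5664) / (0.4779/0.5221) = 0.84; reversed, 1.20.

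With 200 per arm the two-sided 5% test rejects a true null about 7% of the time at 25%/15% and about 14% at 30%/10%.

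With a true effect (50% against 33.3%, odds ratio 0.50) and 20% attrition in both arms, the observed proportions are 45.6% and 30.2% and the odds ratio is 0.52, a negligible change.

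**4. Carrying this to injurious falls.** The protocol gives no 12-month risk for them. For a rare event, leavers are observed for half a year on average, so the observed proportion is about p(1 − a/2). The null odds ratio is then about 0.875/0.925 = 0.95 at 25%/15% and 0.85/0.95 = 0.89 at 30%/10%. The bias for (c) is thus somewhat smaller than the 50%-risk figures.

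**5. Recurrent falls.** Item (a) is one or more falls and (b) is the first fall. The category of two or more under Subgroup analyses is falls history before entry. No item matches the outcome.

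**The case against.** The case against is substantial, and much of it stands.

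- **Most of the list is sound.** A reader might infer that the secondary analyses in general ignore follow-up. They do not: (b) and (f) are survival analyses, and (d) and the scales in (e) are 12-month measures. For any fall, (b) is already the censoring-aware analysis, and reporting a simple proportion beside it is legitimate.
- **The classification of early leavers is not stated.** A reader might infer that the plan counts them as non-fallers. The wording of (a) permits that reading but does not fix it, and the analysis plan mentioned under Data monitoring and analysis is not shown. The bias is therefore conditional.
- **The attrition splits are assumptions.** The protocol gives only 20% overall. Equal attrition unrelated to falling leaves the null odds ratio at 1.00.
- **Records supplement the diaries.** Ascertainment of outcomes provides for checks against GP and hospital records where possible. Fractures or sutured wounds may be found after diaries stop. This reduces the problem for (c) but does not remove it, since monitoring of falls ends at withdrawal or death.
- **Linear regression for service use.** A reader might call this an error because counts have zeros and a log cannot take them. The protocol names no log transform, and linear regression compares mean use, which is defensible.
- **Recurrent falls.** It could be said that single or recurrent simply means any fall, or that the analysis plan will add the comparison. The first reading leaves the cut-off of more than one without a purpose. The second is possible, but the protocol's own list still does not match its outcomes. To say that the question cannot be answered would go too far, because the diaries supply the counts.

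**Conclusion.** Two points hold. First, injurious falls are compared by logistic regression with no allowance for follow-up length, and no other listed analysis covers censoring for them; for any fall, (b) does. Second, recurrent falls have no listed analysis.

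The first matters only if early leavers are classified on observed time and attrition differs between arms. With a 50% risk, constant hazard and uniform dropout, the null odds ratio is then 0.91 at 25% against 15% and 0.84 at 30% against 10%. For a rare injurious fall it is about 0.95 and 0.89. It is 1.00 if attrition is equal and unrelated to falling.

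The second rests on no numerical assumption: it is a mismatch between stated outcomes and stated analyses. Neither point touches the primary analysis, items (d) and (f), or the 12-month scales in (e).

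**What to change.** In Univariate and multivariate analyses:

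1. Make (b) the main between-arm comparison for any fall, with (a) descriptive or supportive.
2. Replace (c) by time to first injurious fall, using a Cox model censored at withdrawal, death or 12 months.
3. Add recurrent fallers (two or more falls) as a listed secondary analysis, using time to second fall with the same censoring.

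As an option only, counts of health-service contacts could be analysed by negative binomial regression with log follow-up as offset.

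The cost is wording and a little more analysis. Follow-up length is already needed for the primary analysis and fall timing for (b). Hazard ratios replace odds ratios for these outcomes. Censoring removes the exposure problem but still assumes that withdrawal is unrelated to fall risk.

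The recurrent-falls comparison will probably be imprecise. With means of 2.0 and 1.5 falls and an assumed negative binomial dispersion from 0.25 to 2.66, the proportions run from 54% against 42% to 34% against 29%. Power for comparing those proportions at 160 per arm runs from about 60% down to 17%. It is best reported as an estimate with its interval.
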